[figure not shown]

**VERSION HISTORY**

| **Version number** | **Version date** | **Reasons for change** |
| --- | --- | --- |
| 1.0 | 2022-01-18 | First version of the study protocol. Submitted to the Swedish Ethical Review Authority. |
| 1.1 | 2022-03-25 | - In section 6.2, we have removed that participants will be encouraged to go the gym or exercise at home, after request from the Swedish Ethical Review Authority, due to insurance-related concerns. - In section 7.2, Cardiometabolic risk, outcome 14), it has been clarified that we are collecting samples on genetic biomarkers. White blood cell telomere length was added to this sentence instead of stated separately as in version 1.0. A corresponding change has been done in Table 2. |
| 1.2 | 2022-06-08 | - We have removed one risk factor from the list of cardiometabolic risk factors in the inclusion criteria: “**Insulin resistance:** Confirmed by the study nurse at the initial cardiometabolic evaluation, after analyzing blood sample collected after >8 h fast, and calculating the Homeostatis Model Assessment Index for Insulin Resistance (HOMA-IR): fasting glucose [mmol/L] × fasting insulin [μU/mL]/22.5. Common reference levels for HOMA-IR insulin resistance range from 0.7 - 2.0.”   The reason for removing it is that it requires a complicated procedure and it is deemed that we would get sufficient information on this variable from the oral glucose tolerance test.   - The 6-month follow-up has been removed and, instead, measures will only be collected at baseline, post-intervention, and at the 3-month follow-up. An amendment has been submitted to the ethical committee to approve this change.   The changes in this version of the protocol have been done before the start of the recruitment. |
| 1.3 | 2022-12-21 | - The oral glucose tolerance test at post-intervention has been removed since glucose levels take longer than 3 months to change, the test takes long time, and it can be perceived as too demanding by the participants. The measures are kept at baseline and at the 3-month follow-up. - We have amended an error in Table 2: Fasting insulin was removed since this was not a planned outcome measure. - In section 9 regarding statistical analysis, it has been clarified that the linear mixed effects regression analyses were for baseline to post-assessment and baseline to the 3-month follow up. It has been added that results would be stratified by gender, power allowing. - Ethical amendments with reference numbers 2022-03546-02, approved 2022-07-11 (referring to change in data collection time points) have been added to page 1. |
| 1.4 | 2024-02-14 | - The list of funders in the cover page of the protocol and in section 14 about the financing sources has been updated. - Ethical amendment with reference number 2023-01962-02, approved 2023-04-06 (referring to prolonging the period to store biobank blood samples) have been added to page 1. - Additional questions have been added to the interview guide (part 2). The questions are now part of the Appendix and this additional set of questions is also described in section 7.4. An ethical amendment with reference number 2024-00708-02 regarding this addition has been approved on 2024-02-14, and added to page 1. |

# SUMMARY

| **Title:** | A structured lifestyle intervention to reduce cardiometabolic risk factors in individuals with obsessive-compulsive disorder – a feasibility study |
| --- | --- |
| **Short title:** | Lifestyle intervention for OCD |
| **Objectives:** | The overall aim of this study is to evaluate the feasibility of a lifestyle intervention to reduce cardiometabolic risk factors in individuals with OCD. Specific aims include to: 1) evaluate the acceptability of the intervention, 2) evaluate its preliminary efficacy, and 3) systematically gather participants’ perspectives and responses to different components of the intervention and how OCD symptoms affect lifestyle habits, the ability to make lifestyle changes, as well as experiences of seeking and receiving somatic health care, in order to further improve the intervention before conducting a large-scale, fully-powered efficacy trial. |
| **Type of trial:** | Single-group feasibility trial |
| **Trial design and methods:** | All potential participants are initially screened via the telephone. This is followed by an inclusion assessment which includes a face-to-face/phone psychiatric interview and an in-person medical assessment to evaluate cardiometabolic variables. Participants who are eligible and have consented to participate will be offered to take part in the intervention which will include 1 individual session with a clinical psychologist and a nurse + 6 psychoeducation group sessions on lifestyle habits + 12 exercise sessions.  Participants will complete measures at baseline, post-intervention, and 3 months post-intervention.  The primary outcome measures are ease of recruitment, participant retention, adherence to the intervention, credibility, safety, and satisfaction with the intervention at post-intervention, which will constitute measures of intervention feasibility and acceptability. Secondary outcome measures include changes in lifestyle habits, cardiometabolic physiological measurements, OCD severity, functional impairment, and quality of life measured at post and 3 months after the end of the intervention. |
| **Rationale for study:** | OCD is a prevalent and impairing disorder. Mortality rates in individuals with OCD are higher than in the general population, as is the risk of metabolic and cardiovascular diseases. These risks remain significant over and above psychiatric comorbidities and shared familial factors, indicating that at least part of this risk could be a consequence of the lifestyles of these individuals (e.g., physical inactivity, unhealthy diet). However, no lifestyle interventions targeting cardiometabolic risk factors for people with OCD have ever been evaluated.  Prior to a fully-powered randomized controlled trial evaluating the efficacy and cost-effectiveness of an intervention to reduce cardiometabolic risk factors in individuals with OCD, a feasibility trial is needed to establish the acceptability and credibility of the intervention, participants’ satisfaction, and potential adverse events, as well as to provide preliminary efficacy data. |
| **Participant time in trial:** | Approximately 6 months. |
| **Total trial duration:** | Approximately 18 months (from enrolment of first participant to last participant’s measurement point). |
| **Planned trial sites:** | Psychiatric assessments will be administered face-to-face at Karolinska Universitetssjukhuset, Solna or on the phone. Physiological assessments will be in-person also at Karolinska Universitetssjukhuset, Solna. The intervention will be held at Karolinska Universitetssjukhuset, Huddinge. Since both the assessments and the intervention require in-person participation, the recruitment will be restricted to the Stockholm Region. |
| **Sample:** | 30 adults with OCD and at least three known cardiometabolic risk factors. |
| **Brief eligibility criteria:** | Eligible participants will be aged 18 years or older and have a DSM-5 diagnosis of OCD and at least 3 cardiometabolic risk factors, out of a predefined list. Exclusion criteria will include language limitations, inability to travel to Stockholm, inability to attend the intervention sessions, intellectual disability or acute psychiatric symptoms or suicidal risk that could interfere with the intervention, being pregnant or breastfeeding, having had a myocardial infarction or stroke within the previous 6 months, cardiometabolic risk measures much over the normal range or initiation or adjustment of any cardiometabolic medication within 3 months prior to assessments. |
| **Statistical analysis:** | *Demographic and clinical data at baseline* will be summarised using descriptive statistics.  *Feasibility and acceptability of the intervention:* Descriptive statistics on ease of recruitment, participant retention, adherence to the intervention, credibility, safety, and satisfaction.  *Preliminary efficacy*: Measures of lifestyle habits, cardiometabolic risk, OCD severity, functional impairment, and quality of life will be analysed through linear mixed models to detect within group change over time. |

# INTRODUCTION

Obsessive-compulsive disorder (OCD) is characterized by obsessions (recurrent and intrusive thoughts, urges or images that cause anxiety) and compulsions (ritualistic behaviors or mental acts that the individual feels an urge to repeat over and over to reduce the distress caused by the obsessions) (American Psychiatric Association, 2013). OCD is one of the most common psychiatric disorders, affecting approximately 2% of the population (Ruscio et al., 2008). It is a disabling disorder and, if untreated, can become chronic. There are well-validated evidence-based treatments for OCD, including cognitive behavioral therapy (CBT) and serotonin reuptake inhibitors (SRIs) (American Psychiatric Association, 2007; NICE, 2006).

Mortality rates in individuals with OCD have shown to be higher than in the general population (Meier et al., 2016), which may be partially explained by a higher risk of dying by suicide(Fernandez [name] et al., 2017; Meier et al., 2016), although it is also likely that the increased premature mortality is related to natural causes (i.e.,, higher rates of health-related problems). Previous investigations by our team have shown a 45% increased risk for cardiovascular and metabolic disorders in OCD, compared to the general population. The risks were the highest for obesity, a broadly-defined group of circulatory system diseases, and type 2 diabetes mellitus (Isomura et al., 2018). Further, individuals with OCD, compared to matched controls without the disorder, have shown to have a moderately higher risk of a broad range of cardiovascular diseases, with the strongest associations for the subtypes venous thrombo-embolism and heart failure (Isomura et al., 2021). In both these studies, the risks remained increased over and above psychiatric comorbidities and shared familial factors. Hence, it is likely that at least part of these described risks are a consequence of the OCD itself and the lifestyles of the individuals with the disorder (e.g., physical inactivity, unhealthy diet).

Cardiovascular diseases are the number one cause of death globally, and can be prevented by addressing risk factors such as tobacco use, an unhealthy diet, obesity, physical inactivity, and harmful use of alcohol (World Health Organization, 2017). Several interventions to change unhealthy lifestyle habits that can contribute to the risk of cardiometabolic disorders have previously been evaluated in the general population. Results indicate that targeting lifestyle factors can lead to changes in indicators of cardiometabolic risk, such as high blood pressure, obesity, and total cholesterol (Lidin et al., 2018; Svetkey et al., 2003). There is also an increasing number of studies targeting lifestyle factors in populations with psychiatric disorders, but these are mainly focused on people with bipolar disorder and psychotic disorders, such as schizophrenia (Cabassa et al., 2010; Green et al., 2015). Results show that these interventions, including for example implementation of a healthy diet and an increase of physical activity, lead to health improvements in the cardiometabolic profile of these patients (Cabassa et al., 2010; Green et al., 2015). However, to our knowledge, no lifestyle interventions targeting cardiometabolic risk factors for people with OCD have ever been evaluated. A few pilot investigations have tested exercise as an adjunct intervention to CBT in order to reduce OCD symptoms, but they were based on small samples (range 11 to 56 participants) (Abrantes et al., 2017; Brown et al., 2007; Rector et al., 2015). In one of these studies, Abrantes et al. (2017) conducted a pilot randomized controlled trial (RCT), including 56 participants, that tested the effect of an aerobic exercise group (n=28) or a health education group (n=28) on OCD symptoms. In this study, cardiorespiratory fitness (maximum oxygen uptake, VO_2_) was one secondary outcome measure and, although the sample was small and underpowered to detect between-group significant differences, results showed a significant increase in VO_2_ in the group on aerobic exercise (i.e., better cardiorespiratory fitness). This indicates that lifestyle interventions can be feasible and acceptable for individuals with OCD.

# Project description

## Design

This feasibility study will use an open trial design with no control group. Quantitative and qualitative data on the feasibility, acceptability, and preliminary efficacy of the lifestyle intervention will be gathered.

## Study sites

The study is a collaboration between the Center for Psychiatry Research (CPF) at the Department of Clinical Neuroscience and the Stockholm Health Services, Region Stockholm, including the Department of Cardiology at Karolinska Universitetssjukhuset, Solna and Psykiatri Sydväst, OCD-programmet at Karolinska Universitetssjukhuset, Huddinge. The screening, initial assessment, and follow-up assessments will take place at an outpatient clinic at the Department of Cardiology, Karolinska Universitssjukhuset, Solna, while the psychoeducation group sessions and exercise sessions will be held at Karolinska Universitetssjukhuset, Huddinge.

## PARTICIPANTS AND SAMPLE SIZE

Participants will be adults meeting criteria for OCD with increased cardiometabolic risk (see definition below; inclusion criterion 3). All inclusion and exclusion criteria are described below. Since the aim of the study is to primarily evaluate the feasibility of the intervention, we do not aim for it to be powered to reveal statistically significant changes in the measures of cardiometabolic risk factors. We aim to include 30 participants to test the feasibility of the intervention. This is a rounded up figure based on the sample sizes in the pilot study by Abrantes et al. (2017) exploring the effect of exercise vs. health education on OCD symptom severity (n=28 in each arm).

## INCLUSION AND EXCLUSION CRITERIA

### Inclusion criteria

1. Aged 18 years or older.

- Confirmed by the participant or assessor at the telephone screening and at the psychiatric assessment.

1. Meeting current criteria for OCD as confirmed by the initial psychiatric evaluation.
   - Screened on the phone and confirmed by the assessor at the initial psychiatric assessment.
2. At least 3 of the following cardiometabolic risk factors:
   1. **Risk alcohol consumption:** >9 units/week or >4 units/occasion for women, >14 units/week or >5 units/occasion for men (Socialstyrelsen, 2018). The information will be collected by asking two self-reported questions: *how many units do you drink every week? how often do you drink 4 (women) or 5 (men) units or more on the same occasion?*
      - Screened on the phone and confirmed by the study nurse at the initial cardiometabolic evaluation.
   2. **Physical inactivity:** <150 min activity/week moderate intensity (i.e., heart beats faster, breathing is faster but able to talk) or <75 min high intensity (i.e., pulse is high, shortened breath, difficulties talking) (World Health Organization, 2020). Evaluated by asking two self-reported questions concerning frequency of weekly moderate or high intensity physical activity and non-exercise physical activity.
      - Screened of the phone and confirmed by the study nurse at the initial cardiometabolic evaluation.
   3. **Unhealthy diet:** Evaluated by asking 5 self-reported questions regarding food habits developed by the Swedish National Board of Health and Welfare, including consumption of vegetables, fruit, fish, sweets/snacks, and breakfast habits (Socialstyrelsen, 2018).
      - Screened on the phone and confirmed by the study nurse at the initial cardiometabolic evaluation.
   4. **Tobacco use (smoking/snuff):**  >1 cigarette/day. Evaluated by asking the following self-reported questions: *do you smoke* (*or did you quit during the last 6 months)? / do you use snuff (or did you quit during the last 6 months)?* If yes: *how many cigarettes per day? / how much snuff?(Socialstyrelsen, 2018)*
      - Screened of the phone and confirmed by the study nurse at the initial cardiometabolic evaluation.
   5. Current or previous **cardiovascular disorder** (except myocardial infarction or stroke within the last 6 months, see exclusion criteria below).

- Screened on the phone and confirmed by the assessor at the initial cardiometabolic evaluation via self-reported interview.
  1. **Abdominal obesity:** Waist circumference **>**88 cm in women, >102 cm in men, according to criteria from the World Health Organization (2011) or sagittal abdominal diameter (SAD): >20 cm in women and >22 cm in men (Risérus et al., 2010).
- Confirmed by the study nurse at the initial cardiometabolic evaluation. Waist circumference measured in a standing position, midway between the lower rib margin and the iliac crest. SAD measured in a supine position at the nearest 0,1 cm with a ruler and a water lever or a calliper, at the level of the umbilical.
  1. **Overweight or obese:** BMI >25 according to criteria from the World Health Organization (World Health Organization, 1995).
- Screened on the phone and confirmed by the study nurse at the initial cardiometabolic evaluation, by calculating the Quetelet index (weight/height^2^). Weight measured on a calibrated scale to the nearest 0.1 kg, height measured barefoot or with thin socks to the nearest 0.1 cm.
  1. **Hypertension:** Systolic blood pressure over 140 mmHg and diastolic blood pressure over 90 mmHg or being currently on medication for hypertension.
- Screened on the phone and confirmed by the study nurse at the initial cardiometabolic evaluation. Systolic and diastolic blood pressure will be measured in a seated position after ten minutes of rest, with a standard sphygmomanometer. The measurement will be taken twice with 1 min between measures, according to the gold standard for measuring blood-pressure (Williams et al., 2018).
  1. **Dyslipidemia:** Elevated total or LDL cholesterol levels or as a high ratio between low density lipoprotein (LDL) and high density lipoprotein (HDL). Total >5.0 mmol/L, LDL >3.0 mmol/L, At risk >1.4 mmol/L (Visseren et al., 2021).
- Confirmed by the study nurse at the initial cardiometabolic evaluation, after analyzing blood sample collected after >8 h fast.
  1. **Impaired glucose tolerance (“prediabetes”):**
     - Confirmed by the study nurse at the initial cardiometabolic evaluation by performing an 2 hour oral glucose tolerance test (OGTT). Reference levels for impaired glucose tolerance is between >7.8 and <11.1 mmol/l according to WHO criteria (World Health Organization, 2006).
  2. **Type 2 diabetes mellitus:** Previous clinical diagnosis or fasting blood glucose levels over 7.0 mmol/l or an OGTT with a 2-hour level 11.1 mmol/l or over.
     - Screened on the phone and confirmed by the study nurse at the initial cardiometabolic evaluation by collecting fasting (>8h) blood sample.

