### exclusion criteria

1. Inability to understand and communicate in Swedish.
   - Confirmed at the first phone screening.
2. Inability to travel to Stockholm for the duration of the intervention.
   - Screened on the phone and/or confirmed by the assessor at the initial psychiatric evaluation.
3. Inability to consistently attend the sessions involved in the intervention.
   - Screened on the phone and/or confirmed by the assessor at the initial psychiatric evaluation.
4. Impairing symtoms of OCD that can interfere with participation in the lifestyle intervention (e.g., inability to travel to group and exercise sessions).
   - Screened on the phone and confirmed by assessor at the initial psychiatric evaluation.
5. Intellectual disabilities or a diagnosis of a psychiatric disorder(s) that can interfere with the intervention, such as acute psychotic or bipolar disorders or severe depression.
   - Screened on the phone and confirmed by the assessor at the initial psychiatric evaluation.
6. A clinical diagnosis of an eating disorder or an alcohol or drug use disorder.
   - Screened on the phone and confirmed by the assessor at the initial psychiatric evaluation.
7. Suicidal risk that may interfere with the intervention.
   - Screened on the phone and confirmed by the assessor at the initial psychiatric evaluation (suicide items on the MINI interview).
8. Pregnancy or breastfeeding.
   - Screened on the phone and confirmed by the assessor at the initial psychiatric evaluation or the cardiometabolic evaluation.
9. Myocardial infarction or stroke within the last 6 months.
   - Screened on the phone and confirmed by the assessor at the initial cardiometabolic evaluation.
10. Cardiovascular risk measures siginificantly over the normal range: e.g., severe hypertension (blood pressure above ≥180 mmHg systolic or ≥110 mmHg diastolic) that makes participation in the intervention contraindicated.
    - Confirmed by the assessor at the initial cardiometabolic evaluation.
11. Initiation or adjustment of any cardiometabolic medication (e.g., blood pressure or blood lipids lowering mediation) within 3 months prior to assessments.
    - Screened on the phone and/or confirmed by the assessor at the initial cardiometabolic evaluation.

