### SCREENING AND ENROLLING

Potential participants that have expressed interest in the study will be first contacted by telephone by the study coordinator for an initial screening of the inclusion/exclusion criteria. Questions will include: OCD diagnosis and OCD symptom severity; psychiatric history; current psychological treatment; cardiometabolic symptoms, including self-reported weight and height to calculate the BMI, brief medical history (cardiovascular disorders, type 2 diabetes), and current medication; and lifestyle habits, including physical activity, smoking/snuff use, alcohol consumption, and dietary habits, which will be screened through a short questionnaire, based on guidelines from the Swedish National Board of Health and Welfare (Socialstyrelsen, 2018).

Participants that are still considered suitable after the first phone screening, will be invited for a face-to-face at Karolinska Universitetssjukhuset, Solna or phone assessment in which the study coordinator will confirm the diagnosis of OCD via the OCD-RD, a short diagnostic interview originally based on the Structured Clinical Interview (SCID) for DSM-IV, which aligns with the DSM-5 criteria for OCD and related disorders. Additionally, severity of the OCD symptoms will be measured by the Yale-Brown Obsessive-Compulsive Scale (Y-BOCS). Comorbid psychiatric disorders and suicide risk will be assessed by means of the MINI (Mini-International Neuropsychiatric Interview;(Sheehan et al., 1998) in order to check whether other inclusion/exclusion criteria are met. This interview will last around 1-1.5 hours.

For those participants with severe OCD that can interfere with the ability to participate in the lifestyle intervention or that have not received optimal treatment for OCD, appropriate referrals will be arranged.

If, after the psychiatric interview, participants still seem potentially suitable for inclusion, they will be invited to an assessment session at the Department of Cardiology at Karolinska Universitetssjukhuset, Solna where a study nurse specialised in cardiovascular disorders will confirm whether current cardiometabolic risk is present, as per the inclusion criteria above. Data will be collected by means of a semi-structured interview, anthropometric measurements, and a blood test. This assessment will last about 1 hour.

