The **group exercise sessions** will be held weekly during the 12 weeks of the intervention; on those weeks with educational sessions, these will be followed by an exercise session. These exercise sessions will be done in the context of the *Braining-project*. Braining consists of group exercise sessions led by mental health staff at Karolinska Universtetssjukhuset, Huddinge. The exercise is of medium to vigorous intensity level and includes both aerobic and resistance training. Each session lasts 30 to 45 minutes. Participation in a minimum of one group exercise session per week is required. However, participants will have the opportunity and will be encouraged to attend more *Braining* sessions (already ongoing at the hospital for other patients with a range of mental disorders) in order to increase the weekly time dedicated to moderately intense physical activity.

After the 12 weeks of lifestyle intervention, participants will be invited to 3 monthly booster sessions (at 1, 2, and 3 months post intervention) to help them maintain their behavioral changes.

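### The contraindication exclusion covers out-of-range risk measures but not diagnosed cardiovascular disease, which inclusion factor 5 admits into required medium-to-vigorous exercise

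*Protocol*

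**What the plan says.** Inclusion criterion 3 asks for "At least 3 of the following cardiometabolic risk factors". The list has 11 items. The fifth is a current or previous cardiovascular disorder, with one carve-out: "except myocardial infarction or stroke within the last 6 months, see exclusion criteria below". No type, severity or stability is specified. The item is "Screened on the phone and confirmed by the assessor at the initial cardiometabolic evaluation via self-reported interview".

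Three of the 11 exclusion criteria are cardiometabolic:

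- Exclusion 9: "Myocardial infarction or stroke within the last 6 months".
- Exclusion 10: cardiovascular risk measures well above normal, with severe hypertension (180 mmHg systolic or 110 mmHg diastolic and upwards) as the only example, "that makes participation in the intervention contraindicated".
- Exclusion 11: any cardiometabolic medication begun or changed in the 3 months before assessment.

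On the cardiometabolic evaluation, Screening and Enrolling says: "Data will be collected by means of a semi-structured interview, anthropometric measurements, and a blood test". The inclusion criteria add blood pressure. A nurse specialised in cardiovascular disorders carries it out at the Department of Cardiology.

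On the intervention, section 6.2 says: "The exercise is of medium to vigorous intensity level and includes both aerobic and resistance training". At least one group session a week is required for 12 weeks, more are encouraged, and mental health staff lead them.

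**The concern.** The protocol accepts that a person's cardiovascular state can make taking part contraindicated, but it writes that principle for measurements only. An extreme reading can exclude a candidate. A diagnosed cardiac disease cannot, and under factor 5 it counts towards eligibility. Such a candidate is foreseeable on the protocol's own account: the Introduction reports, for cardiovascular disease in people with OCD, the "strongest associations for the subtypes venous thrombo-embolism and heart failure".

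Two things are at stake. The first is participant safety in a required exercise programme. The second is the trial's own safety conclusion. The Summary and Objectives list safety among the primary feasibility outcomes, and Implications makes it a condition for going on to the full randomised trial.

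**Working it through.** No calculation in the plan bears on this point. The check takes one candidate through the written criteria.

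Test candidate (assumed): an adult with OCD who meets the age and non-cardiac criteria and discloses current heart failure. There has been no infarction or stroke in the last 6 months. Medication is absent, or unchanged for more than 3 months. Blood pressure is below the severe limits and no other risk measure is far out of range. The candidate is physically inactive and has a BMI over 25.

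**Step 1, inclusion.** Cardiovascular disorder (1) + inactivity (1) + BMI (1) = 3, which meets the minimum of 3.

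**Step 2, cardiometabolic exclusions.**

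| Exclusion | What triggers it | Test candidate |
| --- | --- | --- |
| 9 | Infarction or stroke within 6 months | Not triggered |
| 10 | A risk measure far above normal | Not triggered |
| 11 | Medication started or adjusted within 3 months | Not triggered |

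In exclusion 10 the contraindication wording qualifies the risk measures or the hypertension example. On either reading it does not extend to a diagnosis. The brief eligibility criteria in the Summary also speak only of measures.

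**Step 3, other exclusions.** The remaining eight concern language, travel, attendance, OCD symptoms, psychiatric diagnoses, eating or substance use disorders, suicidal risk, and pregnancy or breastfeeding. The nearest is number 3, on ability to attend consistently. It concerns attendance, and it is settled at the phone screen or the psychiatric evaluation, before the cardiometabolic evaluation takes place.

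**Step 4, what follows.** The candidate must then attend weekly medium-to-vigorous aerobic and resistance sessions. If these are contraindicated for that person, no written criterion lets the assessor say so.

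**Step 5, is factor 5 itself the cause?** Suppose factor 5 is removed and the same person also has an unhealthy diet. Inactivity (1) + diet (1) + BMI (1) = 3, so the person still qualifies. The gap therefore lies in the scope of the exclusions. Factor 5 matters because it shows that people with cardiovascular disease are expected in the sample.

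**Step 6, size.** The document does not give the share of candidates with a current cardiovascular disorder, so the number affected cannot be computed. The only available scale is the planned sample: one event would be 1/30 = 3.3%.

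**The case against.** The strongest reply is that the setting already supplies the judgement. The evaluation is done by a cardiovascular nurse in a cardiology outpatient clinic. The phone screen asks about cardiovascular history and medication. The individual session at the start builds a personal plan from the baseline findings. The example in exclusion 10 is open-ended and leaves some discretion. Adverse events are checked at every educational session, by telephone in the other weeks, and by questionnaire at mid- and post-intervention. Factor 5 and exclusion 9 agree with each other, and including people with cardiovascular disease may be intended and reasonable.

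Most of this stands and lowers the risk. It does not close the gap. The discretion in exclusion 10 is tied to out-of-range measures, the personal plan is made after inclusion, and monitoring acts once exercise has begun.

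A reader might infer four stronger things that the document does not support:

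- *That anyone with active heart disease passes.* Exclusion 11 applies to any cardiometabolic medication and may catch a recent thrombo-embolism or unstable coronary disease, where new or changed medication is plausible. The clear case is a current disorder on unchanged or no medication.
- *That the criteria select for cardiovascular disease.* It is one of 11 factors and nobody needs it to qualify.
- *That reliance on self-report is the hazard.* Someone who discloses a disorder is known to the assessor; what is missing is a criterion to act on.
- *That calling the intervention safe contradicts the infarction cited from another trial.* Ethical considerations gives reasons for its view, also cites a study with no serious study-related events, and promises careful monitoring. The weakness is narrower: the stated basis is national guidelines and interventions in other mental health populations and the general population, and the section does not address participants who already have cardiovascular disease.

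**Conclusion.** The point holds as a mismatch of scope. Factor 5 admits diagnosed cardiovascular disease, section 6.2 requires exercise of up to vigorous intensity, and the only contraindication clause stops at risk measures. A candidate with a current cardiac disorder, acceptable measures and no medication change in the last 3 months meets every cardiometabolic criterion as written, even where the exercise is contraindicated for that person.

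This rests on reading exclusion 10 as written and on the assumption that such candidates come forward. The Introduction makes that plausible, but it gives a relative association and calls the overall excess risk moderate, so it does not show how many there will be. It should be corrected. It does not show that the trial is unsafe.

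**What to change.** Reconcile inclusion factor 5, exclusions 9 to 11, the exercise requirement in section 6.2 and the safety statement under Ethical considerations. The aim is that the protocol's existing contraindication principle covers diagnosed cardiovascular disease as well as risk measures, and that it is judged at the cardiometabolic evaluation already planned. Which conditions count and how they are assessed is for the sponsor's clinical team; this review proposes no clinical rule.

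The cost is an amendment of wording, with no new visit or measurement implied by the wording itself. The downside is that a few candidates may be excluded. If enrolment has already closed, the same reconciliation belongs in the protocol of the planned randomised trial.
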